## Abstract

Supplemental Digital Content is available in the text

## Introduction

1

Functional constipation (FC) is considered a common childhood disease worldwide.^[1]^ It accounts for 3% to 5% of pediatrician visits and 10% to 25% referrals to gastroenterologists.^[2]^ Constipation can be commonly associated with infrequent and/or painful defecation, fecal incontinence, and abdominal pain. It is a cause of psychological stress for the child and family, and it has a significant impact on health care costs.^[1]^

The pathophysiology of constipation in children is multifactorial and is associated with many risk factors and their interactions. Several organic diseases cause constipation. However, in most children presenting with constipation, no underlying causal disease can be found. Thus, over 90% of children with this condition have FC.^[1,3]^ At present, the most commonly used diagnostic criteria for FC are the Rome IV definitions (2016), including clinical signs and symptoms that must be present for at least 1 month.^[4,5]^ A vast majority of children with FC respond to standard medical treatment, including pharmacological and nonpharmacological interventions. Pharmacological treatment with laxatives involves 3 steps: disimpactation, maintenance treatment, and weaning. Nonpharmacological interventions involve education, demystification, guidance for toilet training, scheduled toilet seats, establishing a reward system, and keeping a defecation diary.^[1,6,7]^ However, some children may be refractory to these conventional treatments.^[1,2]^

Over the past 2 decades, neurostimulation has been incorporated in clinical practice to treat a variety of problems, ranging from nausea and vomiting to bowel and urinary disorders.^[8–12]^ Neurostimulation gathers a set of procedures involving the circulation of electric current to obtain physiological responses, depending on its intensity, frequency, and pulse width.^[11]^ Various neurostimulation methods have been introduced to treat both bladder and bowel elimination disorders that are resistant to standard therapy.^[13,14]^

Stimulation of spinal sacral nerves via implantable neuromodulatory therapies such as sacral nerve stimulation (SNS) may improve symptoms of constipation. SNS has been increasingly indicated for severe cases of constipation in adults and children.^[15–17]^ However, SNS is an expensive and invasive method that requires at least 1 general anesthetic with complication rates ranging from 17.2% to 50%.^[13,18,19]^

Transcutaneous electrical nerve stimulation (TENS) may be a promising noninvasive and less expensive alternative to SNS.^[14]^ Transcutaneous stimulation can activate afferent neuronal networks noninvasively, leading to sacral reflexes that may improve colonic motility.^[18]^ A systematic review evaluated the effectiveness and safety of TENS to improve constipation in children.^[20]^ The authors concluded that there is not enough evidence to establish conclusions and suggested that randomized controlled trials assessing TENS for the management of childhood constipation should be conducted, addressing methodology and outcomes.^[20]^

Transcutaneous parasacral nerve stimulation (TPNS) via electrodes placed over the sacrum has been applied to reduce bladder contractility and symptoms in children with overactive bladder.^[21–23]^ Multiple studies have also shown that TPNS is useful for the improvement of fecal incontinence in adults.^[24–26]^ However, its use for the treatment of constipation has been minor investigated. Kim et al^[27]^ found significant improvements in constipation symptoms and the number of bowel movements in a group of 15 adults treated with TPNS. On the other hand, Iqbal et al^[18]^ failed to identify a significant improvement of constipation symptoms in 16 patients submitted to TPNS over 4 weeks for 12 hours a day.

In children, the impact of TPNS on constipation symptoms was assessed only in patients who had a variety of associated underlying causes. Veiga et al^[28]^ found a significant reduction in constipation symptoms in 14 children with lower urinary tract dysfunction after 20 sections of TPNS. In another study, the same group also showed resolution of constipation, according to Rome III criteria, in 15 of 25 children with overactive bladder submitted to TPNS.^[29]^ Martins-Moura et al^[30]^ evaluated 18 patients who had developed constipation on the postoperative evolution of a pull-through procedure for Hirschsprung disease or posterior sagittal approach for anorectal malformation. The authors found remission or improvement of constipation in 15 (83.3%) of these patients after TPNS.

Therefore, TPNS is a minimally invasive, well-tolerated, and accessible technique with the potential to improve constipation in the pediatric population. Thus, we decided to assess the applicability and clinical outcomes of TPNS in children with FC.

## Methods

2

### Study design and setting

2.1

This is a single-center, prospective, longitudinal, and interventional study designed to evaluate the applicability and clinical outcomes of TPNS in children with FC.

This research will be conducted at the Botucatu Medical School, Sao Paulo State University (UNESP), São Paulo, Brazil. The data collection period will be 18 months long, starting in November 2020. Patients will participate in daily sessions of TPNS for a period of 4 or 8 weeks. All patients will also be invited to participate in semi structured interviews at 3 or 4 moments: 1 week before the start of the intervention; immediately after the 4 weeks of intervention or immediately after the 4 and 8 weeks of intervention; and 4 weeks after the end of the intervention period. In these appointments, the aspects related to bowel habits and quality of life will be evaluated.

### Ethics approval and consent

2.2

This study will be conducted according to the principles of the Declaration of Helsinki, ISO14155, Data Protection Act, and the Guidelines for Good Clinical Practice. The Research Ethics Committee (REC) of the Botucatu Medical School, UNESP, São Paulo, Brazil, approved this study, registered under number 13760619.4.0000.5411 (see REC, Supplemental Digital Content 1). Parents or guardians of patients will be informed of the purpose of the study and will sign an informed consent form (see informed consent form, Supplemental Digital Content 2). Patients aged 11 to 18 years will sign the respective specific consent form (see specific consent form, Supplemental Digital Content 3). REC will receive all data at the end of the study. The participants may leave the study at any time without any restrictions.

The Brazilian Registry of Clinical Trials (Rebec) identifier for this study is RBR-52f6h2, obtained on July 6, 2020 (UTN number: U1111-1250-1769) and is available at http://www.ensaiosclinicos.gov.br/rg/RBR-52f6h2/.

### Patient selection and recruitment

2.3

The estimated sample size was 28 patients, calculated for a paired *t*-test (before and after intervention), based on an estimated mean increase of 18 defecations per month (according to data from a previous TPNS study 27), an estimated standard deviation of changes = 30, a 2-tailed α = 0.05 and a test power β= 0.85. The sample will include the Pediatric Gastroenterology Outpatient and Pediatric Surgery Outpatient Clinics of the Botucatu Medical School (UNESP). Patients will be invited to participate in an initial consultation to inform them about the research methods and apply eligibility criteria.

### Eligibility criteria

2.4

The inclusion and exclusion criteria are presented in Table 1.

**Table 1 T1:** Eligibility criteria.

Inclusion criteria	Exclusion criteria
Diagnosis of functional constipation, according to Rome IV criteria (2016) ^[4,5]^	Presence of any organic cause for constipation
Children with age between 7 and 18 yrs old	Children with neurological and/ or cognitive deficits
Patients and/or their guardians who agree to and sign the ICF	Presence of skin lesions in the region of application of the electrodes
Patients aged 11 to 18 who agree and sign the respective SCF	An altered sensation at the electrode application site
Use of cardiac pacemaker	
Children with heart disease or cardiac arrhythmias	
Patients who do not complete the intervention or do not participate in some of the evaluation interviews	

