**Figure 1 F1:**
[figure not shown]
Electrode positioning for transcutaneous parasacral nerve stimulation.

Parents or guardians will be trained to perform TPNS on their children. Training courses and supervised applications will be provided until parents are confident enough to implement TPNS without supervision. From then on, TPNS will be executed daily in the family. During the intervention period, patients will need to attend a supervised session of TPNS every 15 days for a revaluation of the technique and clarification of any doubts.

During the intervention period, patients must maintain all the treatment recommendations (drugs, diets, and behaviors) previously prescribed by the referring physician. Any necessary modifications in treatment during this period will not be avoided or postponed because of the study. Patients must call the research team any changes to the treatment plan during the intervention.

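### Entry requires no period of unchanged background treatment, so improvement from recently started standard care can be counted in the before-after change

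*Protocol article*

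**What the plan says.** Table 1 (Section 2.4, Eligibility criteria) has one disease criterion: "Diagnosis of functional constipation, according to Rome IV criteria (2016"). The other entries concern age, consent, organic causes, neurological or cognitive deficit, skin and sensation at the electrode site, cardiac conditions and non-completion. None concerns earlier treatment, its duration or its failure. The one duration tied to diagnosis is in the Introduction, which describes Rome IV as "including clinical signs and symptoms that must be present for at least 1 month". That is time with symptoms, not time on treatment.

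On standard care the Introduction says: "A vast majority of children with FC respond to standard medical treatment, including pharmacological and nonpharmacological interventions". It adds: "However, some children may be refractory to these conventional treatments".

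Section 2.5 (Intervention) says that during TPNS "patients must maintain all the treatment recommendations (drugs, diets, and behaviors) previously prescribed by the referring physician", and also that "Any necessary modifications in treatment during this period will not be avoided or postponed because of the study". Families must report changes made during the intervention. Section 2.8 has a diary, including laxative use and doses, starting seven days before each assessment. Section 2.9 analyses laxative, clinical and dietary changes as secondary endpoints.

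Section 2.1 describes the design: "This is a single-center, prospective, longitudinal, and interventional study designed to evaluate the applicability and clinical outcomes of TPNS in children with FC". No control group is described. Baseline is one interview a week before TPNS (Section 2.7), time points are compared with paired tests (Section 2.10), and the Discussion states an aim of demonstrating efficacy.

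**The concern.** A child may enter whose laxative, diet or toilet programme began shortly before the baseline interview. If that treatment is still taking effect, its benefit falls in the same 4 or 8 weeks as TPNS and in the same direction as the hoped-for result. With no concurrent control, it is added in full to the mean paired change.

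Holding the prescription constant during TPNS does not prevent this, because a constant prescription can have an effect that is still growing. Nor do the rules on reporting and analysing changes deal with it: they are directed at changes during the study, and a regimen begun before baseline and then kept is not such a change. If the improvement lasts, the interview 4 weeks after the end of treatment would also read it as a remaining effect of TPNS.

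At stake is how much of a significant increase in stool frequency can be credited to TPNS. The protocol's own statement that most children respond to standard care makes this source of improvement a plausible one.

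**Working it through.** **Inputs from Section 2.3:** n = 28, target mean increase 18 defecations per month, SD of changes 30, two-sided α = 0.05, power 0.85, paired t-test.

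**Reproducing the plan's figure.** The normal approximation is n = [SD × (z₀.₉₇₅ + z₀.₈₅) / δ]² = [30 × (1.960 + 1.036) / 18]² = 24.9. The exact paired t-test (noncentral t) needs 27, with power 0.851, and at n = 28 the power is 0.864. The stated 28 is therefore sound. The point concerns bias, not sample size.

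**Assumptions not in the document.** TPNS has no effect. A share f of children are still responding to recently started care, and each gains on average g defecations per month from it. The rest gain nothing on average.

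**Formulas.**
- Spurious mean change: m = f × g.
- SD of change, allowing for the mixture: s = √(30² + f(1 − f)g²).
- Noncentrality: m/s × √28, with 27 degrees of freedom and critical value 2.052.

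**Worked example,** f = 0.50, g = 18: m = 9.0. s = √(900 + 0.25 × 324) = √981 = 31.3. Noncentrality = 9.0/31.3 × 5.292 = 1.52. The chance of p < 0.05 is 0.311.

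| Share f | Gain g per month | Spurious mean gain | Share of the target of 18 | Chance of p < 0.05 |
|---|---|---|---|---|
| 0 | – | 0 | 0% | 5% |
| 10% | 9 | 0.9 | 5% | 5.3% |
| 20% | 9 | 1.8 | 10% | 6.1% |
| 20% | 18 | 3.6 | 20% | 9% |
| 50% | 9 | 4.5 | 25% | 12% |
| 50% | 18 | 9.0 | 50% | 31% |
| 75% | 18 | 13.5 | 75% | 60% |

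Holding the SD at 30 in spite of the mixture would give 33% and 63% in the last two rows. The wider SD is the more careful choice.

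**Cost of restricting the main analysis to stable children.** If half the children are recent starters, 28 × 0.5 = 14 remain. Power for a change of 18 with SD 30 then falls from 0.86 to 0.55.

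**The case against.** Several objections carry weight.

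- **Recent starters may be few.** A reader might infer from the specialist clinics that children arrive newly referred and newly treated. The document does not say so. Section 2.3 names two outpatient clinics and gives no time under care, and Section 2.5 speaks of treatment already prescribed, which suggests that children come with a treatment history. The text permits recent starters without showing that they are common. At shares of 10% to 20% with a gain of 9 the inflation is negligible. This stands, and it is why the size is a range.
- **Some information may be captured.** The diary would show a laxative started within the baseline week. The clinical-status questionnaire (Supplemental Digital Content 4) is not shown and may ask about treatment dates. The list of secondary conditions in Section 2.9 is open-ended. It would therefore be too strong to say that nothing could reveal the problem. But none of these restricts entry, and the protocol text does not describe a date of start or last change.
- **The study was not meant for refractory children.** A reader might infer such a restriction from "Various neurostimulation methods have been introduced to treat both bladder and bowel elimination disorders that are resistant to standard therapy". That sentence is background. The objective is applicability and clinical outcomes in functional constipation, so the lack of a treatment-failure criterion is not a contradiction.
- **The missing control is the larger problem.** This is true: natural course, regression to the mean and expectation remain whatever the entry rule. The entry rule deals with one identifiable component that can be reduced cheaply.

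**Conclusion.** The concern holds in a limited form. Table 1 sets no stable-treatment period, and the safeguards in Sections 2.5, 2.8 and 2.9 do not stand in for one. Improvement from recently started standard care can therefore enter the single-group paired change.

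The size is unknown, because the share of such children and their gain are assumptions. Over the scenarios shown, the chance of a significant result with no TPNS effect runs from about the nominal 5% to 60%. The upper figure needs three quarters of the children each to gain as much from standard care as the study plans for TPNS. The documents do not support the inference that the result will be badly biased. They support only that the design leaves this open and cannot correct for it afterwards unless treatment dates are known.

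The sample size of 28 is not affected. This is a worthwhile, inexpensive improvement to the design.

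**What to change.** 1. Add to Table 1 a pre-specified minimum period of unchanged background constipation treatment (drugs, diet, toilet programme) before the baseline interview. The investigators should set and justify the length. The 4-week intervention window is one candidate minimum, but nothing in the document shows that 4 weeks is long enough for the effect of standard care to level off. Defer the baseline interview of a child who does not yet meet the period, and leave the child's care to the referring physician.
2. In any case, record at baseline the date on which treatment was started or last changed.
3. Pre-specify a sensitivity analysis reporting the before-after change in stool frequency by time since that date. It should not replace the main analysis, given the loss of power shown above.
4. Word the efficacy conclusion to acknowledge that, without a control group, regression to the mean and natural course are not separated from the effect of TPNS.

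The cost is an amendment with one eligibility line and one date field, and a later start for some children. No accrual rate is given, so whether the deferrals fit within the 18-month collection period should be checked. No visit or procedure is added.

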### Adherence to treatment and related adverse events

2.6

The biweekly-supervised TPNS sessions will be registered by the studies, also investigating the possibility of adverse events. During the research process, patients/parents/guardians can contact the research team by phone to communicate possible adverse events and clarify any questions.

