### Intervention periods and assessment time points

2.7

The intervention period will be 4 consecutive weeks, immediately following the conclusion of the training period. Then, patients and/or their guardians may choose to extend the intervention period for another 4 consecutive weeks until completing 8 weeks of TPNS. The 3 or 4 moments for assessment interviews will be the following: 1 week before the start of the intervention, immediately after the 4 weeks of intervention or immediately after the 4 and 8 weeks of intervention, and 4 weeks after the end of the intervention period, to identify any remaining effects of TPNS.

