### Assessment interviews

2.8

In all assessment moments, patients and/or their guardians will participate in semi-structured interviews to determine the results of interventions regarding bowel movements and quality of life. The same member of the research team will be responsible for the interviews that will last approximately 40 minutes. The following surveys will be applied: a questionnaire addressing the current clinical status developed by our research group and previously used in another study that evaluated the impact of transcutaneous posterior tibial nerve stimulation in children and adolescents with FC^[31]^ (see questionnaire, Supplemental Digital Content 4); the modified Bristol Stool Form Scale for children (mBSFS-C)^[32–34]^ to analyze the stool consistency (see mBSFS-C, Supplemental Digital Content 5); the Bowel Function Score (BF-S)^[35]^ to evaluate the functional status of bowel habits (seeBF-S, Supplemental Digital Content 6); the Fecal Continence Index (FCI) questionnaire,^[36,37]^ based on the clinical evaluation of fecal continence (see FCI, Supplemental Digital Content 7); the Assessment of Quality of Life in Children and Adolescents with Fecal Incontinence (AQLCAFI)^[36,37]^ (see AQLCAFI, Supplemental Digital Content 8) and the Pediatric Quality of Life Inventory version 4.0 (PEDsQL 4.0)^[38,39]^ to assess the quality of life (see PEDsQL 4.0, Supplemental Digital Content 9). Lastly, a questionnaire addressing the evaluation of the applicability of the TPNS daily home sessions^[31]^ also developed and already used by our research group (see applicability questionnaire, Supplemental Digital Content 10).

In addition, patients will be monitored using a standardized week diary (stool frequency, stool consistency according to the mBSFS-c, frequency of fecal incontinence episodes, painful defecation, abdominal pain, excretion of blood in the stool, laxative use and their doses, and adverse effects such as pain, nausea, vomiting, diarrhea, and flatulence). The fulfilment of this diary will start seven days before each assessment moment. The doses of laxative medications will be registered, addressing any alterations as possible outcomes in the study's conclusion.

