### Outcomes

2.9

Data analysis will focus on each assessment moment. The following clinical variables will be used for this analysis: the number of bowel movements per week, the number of fecal incontinence episodes per week, whether diapers or underwear protection is needed, whether defecation medications are needed, special diets, straining and pain while passing stool, presence of fecalomas, presence of abdominal pain, presence of bloody stools, need for enemas, and presence of perianal rashes or dermatitis. We will also analyze the results obtained by all the assessment instruments applied (mBSFS-C, BF-S, FCI questionnaire, AQLCAFI, and PEDsQL 4.0) to evaluate the outcomes of the functional status of bowel habits and the global quality of life.

As a secondary outcome, the applicability of TPNS will also be evaluated through the results of a specific questionnaire^[31]^ (see applicability questionnaire, Supplemental Digital Content 10), taking into account the practical difficulties and possible adverse events involved in using the method. All conditions that may be indirectly involved in the clinical results of TPNS, such as modifications in laxative doses or any clinical or dietary changes, will also be analyzed as secondary endpoints. Figure 2 summarizes the stages of the study and the Supplemental Digital Content 11 (SDC-11) features information about the Standard Protocol Items: Recommendations for Interventionist Tests (SPIRIT).

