### Protocol amendments

2.11

REC will approve any modifications in the study before implementation. Data and source documents will be stored so that they can be accessed later by the REC. At the end of the study, the results will be submitted for publication in a peer-reviewed journal, following CONSORT compliance guidelines. Authorship of any related presentations or reports will be under the name of the collaborative group.

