## Discussion

3

TPNS can be considered a promising, noninvasive, and safe method to be used as adjunctive therapy for treating constipation.^[18,27–30]^ However, there is a lack of published data that has investigated its use directed to treatment of children with FC.

This study's main objective was to assess the applicability and clinical outcomes of TPNS in children with FC. This study aims to demonstrate the efficacy of this promising method to increase the number of bowel movements and to improve stool consistency, to reduce the number of episodes of retentive fecal incontinence and to improve the overall quality of life indirectly.

Our research group has already developed a similar study to evaluate the applicability and clinical results of posterior tibial nerve stimulation in children with functional constipation.^[31]^ Thus, it will also be possible to compare the results obtained by these 2 minimally invasive neurostimulation methods in this clinical setting.

This study is currently in the planning phase, with the recruitment phase planned to begin in November 2020.

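### Table 1 makes completing treatment and attending interviews a condition of eligibility, so applicability would be judged on completers only and would look too favourable

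*Protocol article*

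**What the plan says.** The last row of Table 1 (section 2.4) names "Patients who do not complete the intervention or do not participate in some of the evaluation interviews". The table's columns are shifted in the text available, but the row follows the pacemaker and heart disease rows and makes sense only as an exclusion. Section 2.3 applies the eligibility criteria at an initial consultation.

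Early stopping is foreseen. Section 2.2 states: "The participants may leave the study at any time without any restrictions".

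Applicability is a secondary outcome in section 2.9, measured by questionnaire, "taking into account the practical difficulties and possible adverse events involved in using the method". The Discussion nevertheless places applicability in the main objective, beside clinical outcomes. Section 2.8 gives that questionnaire at the assessment interviews. Section 2.7 sets the interviews during treatment "immediately after the 4 weeks of intervention or immediately after the 4 and 8 weeks of intervention". The diary, which also records adverse effects, is intermittent: "The fulfilment of this diary will start seven days before each assessment moment".

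Adverse events have a further route in section 2.6: "The biweekly-supervised TPNS sessions will be registered by the studies, also investigating the possibility of adverse events". Families may also report them by phone.

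**The concern.** An eligibility criterion should be decidable before treatment. This one depends on what happens during and after it, so it selects the sample on a result of the intervention.

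That matters most for applicability. Parents give stimulation at home every day for 4 or 8 weeks, and whether families can keep this up is much of what the study wants to learn. A family that stops because of discomfort, or because the routine was unworkable, is strong evidence on that question. The rule removes that family and keeps those who managed. The row also catches a child who had every session but missed the follow-up interview. Read literally, it may catch one who finished 4 weeks, chose to extend to 8 and stopped at week 6.

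At stake is a conclusion that the method is easy to use and well tolerated, drawn only from those for whom it was.

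**Working it through.** **Inputs.** Planned sample 28, mean increase 18 defecations per month, SD of changes 30, two-sided alpha 0.05, power 0.85 (all section 2.3). The documents give no stopping rate and no adverse-event rate.

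**The plan's own figure.** Standardised effect d = 18/30 = 0.6. By the exact noncentral t calculation for a paired t-test, n = 27 gives power 0.851 and n = 28 gives 0.864. The stated 28 is therefore sound, and this point does not depend on it.

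**When a stopping child could supply data.**
- The first interview on treatment comes after week 4, at the end of day 28.
- The diary for it starts seven days earlier, on day 28 − 7 + 1 = 22.
- A child who stops on days 1 to 21 therefore reaches neither the on-treatment diary nor the applicability questionnaire.
- What remains for that child is training (supervised applications before day 1), the supervised session at about day 15, and any phone call. These can record an event.
- Table 1 then excludes the child. No section of the article returns an excluded child to the applicability or adverse-event results.

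**Illustration (s is assumed).** Suppose 28 children start, s stop because of an adverse effect, and no completer has one. The rate in treated children is s/28; the rate in completers is 0/(28 − s).

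| s | All treated | Completers only |
|---|---|---|
| 1 | 1/28 = 3.6% | 0/27 = 0% |
| 2 | 2/28 = 7.1% | 0/26 = 0% |
| 3 | 3/28 = 10.7% | 0/25 = 0% |
| 4 | 4/28 = 14.3% | 0/24 = 0% |

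The zeros follow from the rule: an event that made a child stop cannot appear among completers.

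If 2 completers also have an event and s = 4, the rates are 6/28 = 21.4% (exact 95% CI 8.3 to 41.0) in all treated and 2/24 = 8.3% (1.0 to 27.0) in completers.

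**The case against.** The strongest reply is that the row names no analysis set and does not mention safety. It may be meant only for the paired before-after tests in section 2.10, where a child without a later value cannot contribute a pair. Analysis sets are usually left to a full protocol or SAP, which are not shown, and the patient flowchart (Figure 2) and supplements are not visible either. Section 2.2 sends all data to the ethics committee, and section 2.11 commits the report to CONSORT.

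Part of this stands. A reader might infer that adverse events in children who stop are lost altogether. The documents do not support that: section 2.6 collects events during treatment whether or not the child completes. What they support is narrower: an event may be recorded, but the printed rule excludes the child and no exception is stated. The reply does not remove that. The row is an explicit rule, not an omitted detail, and it is placed under eligibility, not under the paired analysis. Neither the data transfer nor the CONSORT commitment says who is counted in the results.

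A reader might also infer that a completers-only confidence interval would demonstrably miss the true rate once four children stop. That is too strong. With 28 enrolled, the exact upper limit for 0/24 is 1 − 0.025^(1/24) = 14.25%, against 4/28 = 14.29%. With 28 completers, the limit for 0/28 is 12.34%, against 4/32 = 12.5%. These margins are hairline, the number stopping is assumed, and 4/28 itself has an interval of 4.0% to 32.7%.

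**Conclusion.** The point holds. As written, Table 1 conditions the sample on completing treatment and attending the interviews. Applicability would then be estimated without the children who found the method hardest to tolerate or use, and the bias runs in the favourable direction.

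Its size cannot be derived from the documents. The 3.6% to 14.3% range for 1 to 4 of 28 children is an illustration, and it concerns only events that led to stopping. The conclusion assumes that the row is applied as printed and that no unseen document restores excluded children to the results. It deserves correction but does not undermine the sample size.

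**What to change.** Delete the last row of Table 1 and treat these children as withdrawals. Report adverse events, discontinuations with date and reason, and applicability for every child given at least one stimulation, training applications included. Count non-completion as an applicability result.

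When a child stops, offer the applicability questionnaire to families willing to answer. It has to be optional, since participants may leave without restriction.

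For the before-after tests, a child lacking a given later value is left out of that comparison only, and the number left out is stated.

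The cost is a small amendment. Section 2.11 says "REC will approve any modifications in the study before implementation", and the Discussion says "This study is currently in the planning phase, with the recruitment phase planned to begin in November 2020", so by the article's own account the change comes before any child is treated. The downsides are some missing questionnaires, some answered by phone instead of at interview, and possibly a less favourable applicability figure. The sample size and the 7-day diary can stay as they are.
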